### Randomization and Blinding

Participants will be randomly assigned to either the intervention or waitlist control group using a computer-generated randomization procedure. The Random Allocation Software developed by [name] [52] will be used to facilitate this process. Block randomization will be implemented to ensure balanced group sizes, with a maximum of 8 participants per group. Randomization will be carried out by an independent researcher who is not part of the current research team or is listed as an author. The principal investigator remains blinded to group assignments to maintain objectivity and reduce potential bias. Outcome measures are managed by a separate research assistant who is not involved in the delivery of the intervention, ensuring independence and reducing potential bias. Once a sufficient number of eligible participants have been recruited, randomization will be conducted, typically 2 weeks before the intervention start date. Participants will then be informed of their group allocation, along with the schedule of their assigned group sessions, by the designated research assistant. In alignment with the ongoing recruitment process and rolling admission, the intervention will be delivered to participants as they are randomized and assigned to groups.

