### Description of the Intervention

The project consists of 5 weekly sessions: 1 introductory (preassessment) session followed by 4 psychoeducational sessions. Each session lasts approximately 60-90 minutes.

In the introduction session, participants sign the informed consent forms after being informed about the program’s content and expectations by the main group facilitator (ie, the research assistant). For participants under 18 years of age, parental consent will also be obtained during the session. Following the signing of consent, the baseline survey will be distributed and collected. Participants’ demographic information will be gathered through the survey. This includes, but is not limited to, age, gender, education level, household income, region of residence, living arrangement, and employment status.

Each week, participants will receive WhatsApp (Meta Platforms, Inc.) text message reminders about upcoming sessions and other important announcements.

The psychoeducational sessions differ in theme but follow a similar structure. Session 1 focuses on emotions located in various quadrants of the 2D model, such as high-arousal and negative-valence emotions. Session 2 explores happiness and loneliness, with the new component of loneliness added to this session. Sessions 3 and 4 address high-arousal emotions, such as stress and anxiety. An example session plan is provided in Multimedia Appendix 1 for reference (Table 1).

**Table 1 table1:** Summary of session content.

Session	Content
Session 1	Emotions located in various quadrants of the 2D model, such as high-arousal and negative-valence emotions
Session 2	Happiness and loneliness
Session 3	High-arousal and negative-valence emotions, such as stress and anxiety
Session 4	High-arousal emotions, such as perfectionism and anxiety (continue) and achievement

For the new loneliness component, in addition to discussing songs that evoke a sense of receiving empathy, psychoeducation will be provided on the positive effects of music sharing in building and strengthening emotional bonds in relationships [12]. The group sessions will offer a safe and pleasant environment where participants can talk about music, using this topic as a channel to foster new connections with fellow group members. In session 2, participants will be guided to discuss how they can apply this skill outside of the program to strengthen existing relationships and build new connections.

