### Additional Measure

We will use the Music USE (MUSE) Questionnaire [59] to assess each participant’s typical music listening habits, including whether they play a musical instrument and if they have received formal musical training. This scale was successfully used in a study involving 1318 adolescents in Hong Kong [34], making it a valuable tool for describing participants’ engagement with music.

For demographic information such as gender and socioeconomic status collected in the survey, tests will also be conducted across the 2 conditions to examine whether the results differ.

The effect of the intervention on reducing anhedonia will also be explored using the Chinese version of the Snaith-Hamilton Pleasure Scale [60]. Data collected from this scale will be used for future outcome analysis.

The Tuned In program’s acceptability among Hong Kong adolescents will be examined using a combination of quantitative and qualitative approaches. Satisfaction ratings will be collected from participants using a 7-point Likert scale. With “strongly disagree” at 1 point and “strongly agree” at 7 points, the ratings will capture the extent to which participants agree with the positive statements. The questions will address the perceived usefulness of the program, the level of interest in the program, the likelihood of recommending the program to other adolescents, and the likelihood of continuing to use music as an emotion regulation strategy in the future [25]. The aforementioned areas of investigation regarding the project’s acceptability are framed into 4 separate rating questions, all of which are included in the postintervention survey. The quantitative questions are provided in Multimedia Appendix 3.

In addition, we will include open-ended qualitative questions to gather feedback from participants on their experiences with the program and to collect suggestions for improvements for a future RCT. Written responses are expected from participants. As feasibility indicators, we will also record the recruitment rate and dropout rate for this trial. The qualitative questions are incorporated into the postintervention survey, to be completed by participants at the end of the final session.

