### Data Analysis

For the main outcome evaluation measures, mixed measures ANOVAs will be performed. The between-participants factor is group (intervention vs control), and the within-participants factor is time (pre- vs postintervention). Before the main analyses, independent samples *t* tests (2-tailed, paired) will be conducted on the baseline demographic variables to identify any significant differences between the 2 groups. Any variables that show statistically significant differences will be included as covariates in the subsequent main analyses. It is expected that the treatment group will demonstrate improved emotion regulation and reduced mood symptoms and loneliness following the music intervention, compared with the control group. A medium effect size is anticipated for the significant group × time interaction effect.

All verbal and written feedback will be analyzed using thematic analysis [61]. The qualitative analysis software NVivo (QSR International) will be used to assist with the process. Content analysis will be conducted following the transcription and coding of the data.

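### Covariates for the main analyses, including the primary DERS analysis, are chosen by baseline significance tests between randomised arms, so the model is unknown until the data are seen and adjustment gains essentially no precision

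*Protocol article*

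**What the plan says.** The Data Analysis section of the protocol article sets the main model: "For the main outcome evaluation measures, mixed measures ANOVAs will be performed", with group as the between-participant factor and time (pre, post) as the within-participant factor. The section on the primary outcome names the DERS as the primary measure, so this model is the primary analysis.

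Before that model is fitted, tests "will be conducted on the baseline demographic variables to identify any significant differences between the 2 groups". The test is specified thus: "independent samples *t* tests (2-tailed, paired) will be conducted on the baseline demographic variables". The result then decides the model: "Any variables that show statistically significant differences will be included as covariates in the subsequent main analyses". No covariate is named in advance.

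Description of the Intervention lists the demographics collected in the baseline survey: "age, gender, education level, household income, region of residence, living arrangement, and employment status". The list is introduced by "This includes, but is not limited to". Allocation is computer-generated, and under Randomization and Blinding "Block randomization will be implemented to ensure balanced group sizes".

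**The concern.** A covariate earns its place in the analysis of a randomised trial by predicting the outcome, or by being part of the design. A test of the baseline difference between arms measures neither. It has the same chance of a significant result for a variable that strongly predicts DERS change as for one that is pure noise. The rule will therefore usually leave out a useful covariate and sometimes bring in a useless one.

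Two things are at stake. The primary model is not fixed before the data are seen, although the article presents the rule as settled. And the trial gives up the precision that adjustment can bring.

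The selection step is also badly specified. Two arms made up of different people cannot give a paired test. Gender, region, living arrangement and employment status are categorical, so a t test does not suit them. The analyst would have to improvise at the very step that decides the primary model.

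**Working it through.** **Inputs from the protocol article**
- Partial eta squared 0.076, P<.05 for the group × time interaction, at least 98 participants, 15% attrition, about 50 adolescents and 65 young adults (Sample Size Calculation).
- Seven named demographics (Description of the Intervention).
- At most 8 participants per group; allocation disclosed after randomisation, typically 2 weeks before the intervention starts (Randomization and Blinding).

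**Assumptions, not in the article:** 80% power; two-sided 5% for each baseline test; independent demographics; one of the seven correlating 0.3 or 0.5 with the DERS change score.

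**1. The plan's own figure.** f² = 0.076/(1 − 0.076) = 0.0823, so f = 0.287 and the equivalent standardised difference is 2f = 0.574. With a noncentral F on 1 and N − 2 degrees of freedom and noncentrality N·f², N = 98 gives 80.3% power. The stated 98 is reproduced, and this point does not disturb it.

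**2. Chance that the rule changes the model.** With k independent tests at 5%, the chance that at least one is significant is 1 − 0.95^k.
- k = 7: 1 − 0.95^7 = 0.302, with 7 × 0.05 = 0.35 covariates expected to enter.
- k = 10 (hypothetical, were three more collected): 1 − 0.95^10 = 0.401.

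The chance that one given variable enters is 5%, whatever its prognostic value.

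**3. What the rule does to the test.** Simulation of the change score, 49 per arm, seven independent covariates of which one is prognostic, 6,000 runs per scenario, standardised effect 0 or 0.574:

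| Correlation with change | Quantity | No covariate | Plan's rule | Prognostic covariate prespecified |
|---|---|---|---|---|
| 0.3 | Type I error | 4.8% | 4.6% | 4.6% |
| 0.3 | Power | 80.7% | 80.2% | 84.1% |
| 0.5 | Type I error | 5.0% | 4.3% | 5.0% |
| 0.5 | Power | 80.4% | 80.4% | 90.1% |

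At least one covariate entered in 30% to 31% of runs, and the prognostic one in about 5%. With no treatment effect and correlation 0.5, the standard deviation of the estimated effect was 0.202 unadjusted, 0.197 under the rule and 0.175 with the covariate prespecified. The rule cuts it by (0.2016 − 0.1966)/0.2016 = 2.5%; prespecification cuts it by (0.2016 − 0.1751)/0.2016 = 13%. The simulation error on a 5% rate is √(0.05 × 0.95/6000) = 0.3 percentage points, so the 4.3% lies below 5% by more than noise, while the 4.6% is close to it.

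**4. Order of events.** Participants are randomised and told their arm, typically 2 weeks before the intervention. The baseline survey is completed later, at the introductory session. Sample Size Calculation allows for dropouts before the intervention begins. A baseline difference could therefore reflect loss after disclosure as well as chance.

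**The case against.** The strongest reply is that the rule does almost no harm compared with the unadjusted ANOVA: power is the same and type I error is, if anything, slightly low. That stands. The loss is a forgone gain, and its size rests on correlations of 0.3 to 0.5 that the article does not supply. In a self-described pilot this keeps the point at moderate weight.

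It can also be said that not every imbalance is chance, because baseline is measured after allocation is disclosed. This stands too, but it does not rescue the rule: a significance test neither identifies the variables that drive such loss nor repairs it.

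The word 'paired' is probably a slip, since the same sentence speaks of independent samples and two groups. Agreed: it needs correcting but does not by itself touch the primary model. The open-ended list of demographics is ordinary condensation in an article and is not held against the plan, except that seven is a minimum.

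The section Additional Measure says that for demographics such as gender and socioeconomic status "tests will also be conducted across the 2 conditions to examine whether the results differ". A reader might take this as a second commitment to baseline testing. It could equally mean comparing outcomes across demographic groups, so nothing here rests on it.

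An unseen analysis plan does not answer the point, because the article states the rule outright.

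**Conclusion.** The point holds in a limited form. Baseline significance decides the covariates of the primary DERS model. That leaves the model open until the data are in and gives essentially no gain in precision: about 80% power with or without the rule, against 84% to 90% for a prespecified covariate under the assumed correlations. The chance that at least one covariate enters is about 30%, if the seven demographics are independent and tested at 5%; correlation among age, education, employment and living arrangement would lower it.

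A reader might infer three stronger things, none supported:
- that test-then-adjust inflates false positives, when the simulated rate was 4.3% to 4.6%;
- that 30% is the chance of a changed conclusion, when it is only the chance that a covariate enters;
- that every significant baseline difference must be chance, which the order of disclosure and baseline survey does not allow one to say.

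Neither the sample size of 98 nor the validity of the trial is in question.

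**What to change.** In Data Analysis:
- Delete the significance-based covariate rule and the baseline tests, and present baseline characteristics descriptively by arm.
- Name a short covariate set in advance, on prognostic or design grounds: the baseline value of the outcome, and recruitment stream (secondary school or university). The article already plans the two streams separately and, under Contingency Plan, expects some attrition among adolescents.
- To use the baseline score as a covariate, analyse the post score by ANCOVA in place of the group × time ANOVA. The baseline score is already a level of the time factor there, so it cannot simply be added.
- Randomisation batch is optional. If each batch fills one group of up to 8 per arm, 115/16 = 7.2 means at least 8 batches and 7 further parameters, and the article gives no evidence that batch is prognostic.
- If any between-arm test is kept, remove the word 'paired' and use a test for categorical data where the variable is categorical.

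The cost is a small change of model specification, not wording alone. With 98 analysed, ANCOVA with arm, baseline score and stream leaves 98 − 4 = 94 residual degrees of freedom, against 96 for the interaction test. Trial conduct and sample size do not change.

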## Results

The successful funding outcome of this project was announced in February 2023. Participant recruitment began in January 2024, and as of September 16, 2024, a total of 316 responses had been received through Qualtrics. Upon submission of the questionnaire, all participants are promptly notified of its receipt. Those deemed eligible receive a basic information sheet, while individuals who are ineligible are provided with a list of supporting resources. Of the responses received, 89 participants were considered eligible for the program. The project is scheduled to conclude in August 2025, with results to be published thereafter.

## Discussion

### Expected Findings

This proposal focuses on examining the short-term impact of a music-based emotion regulation program for young people in Hong Kong. For this trial, we expect the intervention group to demonstrate improved emotion regulation and reduced mood symptoms and loneliness after completing the Tuned In program, compared with the control group. This expectation is based on previous successful trials of Tuned In conducted in Australia [27]. Furthermore, in line with the Transdiagnostic Emotion Vulnerabilities Model, enhanced emotion regulation may help alleviate a range of mood-related issues [7].

Qualitatively, we expect that participants will describe their reduced loneliness and enhanced mental well-being as being directly and indirectly related to music. For example, they may resonate with the music and experience a sense of being understood [12]. We also anticipate that participants will appreciate the use of self-selected music throughout the program [21]. In the future, we plan to conduct longitudinal studies to examine the medium- to long-term impacts of the intervention.

### Strengths

The study demonstrates notable strengths, including the involvement of 2 cofacilitators—a registered music therapist and a trained research assistant with a mental health background—ensuring both clinical expertise and research rigor in program delivery. Additionally, the inclusion of a new session component specifically targeting “loneliness” enhances the intervention by building upon and extending the established “Tuned In” program previously conducted in Australia, thereby addressing an important psychosocial issue with a tailored and evidence-informed approach.

### Limitations

As this study is a pilot RCT, the primary focus is on assessing the feasibility and effectiveness of the intervention. The long-term effects can be explored in future, larger-scale trials. It is acknowledged that the outcome measures used are self-reported. This method was chosen to capture participants’ subjective experiences and perceptions. Additionally, the study does not account for individual differences that may influence outcomes. Factors such as the impact of life events or levels of alexithymia may potentially influence the outcomes of the program and should be taken into account in future research. Subsequent studies could incorporate additional forms of assessment, such as physiological measures or reports from family members, to provide a more comprehensive and corroborated evaluation.

As coping through emotions mediates the relationship between resilience and youth well-being [62], equipping young people with adaptive strategies to manage stress and difficult emotions helps consolidate learning and builds greater internal resources and capacity. This, in turn, positively influences both their short- and long-term mental health. Healthy coping also acts as a protective factor for their future emotional well-being.

Although this project does not investigate the medium- to long-term effects of the intervention on youth mental health due to resource constraints, future research could adopt a longitudinal perspective to explore the factors that help sustain the positive outcomes. Future studies could also incorporate an active control design and examine the individual contribution of each component to the overall effectiveness of the program.

### Conclusions

This project aims to examine the short-term effects of a music-based emotion regulation program for young people in Hong Kong. We expect positive outcomes from this trial, and the preliminary results will inform the planning of future studies to better understand the underlying mechanisms and longer-term impacts.

From a practical perspective, the project will provide valuable insights into the use of music and psychoeducation in youth mental health work in Hong Kong. From a research and theoretical perspective, it may offer evidence regarding the effectiveness of combining music, psychoeducation, and group work in improving youth mental health. Building on the current project, future studies are encouraged to explore innovative ways to enhance the cost-effectiveness, outcome magnitude, reliability, and sustainability of the intervention.

## Appendix

Multimedia Appendix 1 Tuned In group session plan (session 5).

Multimedia Appendix 2 Project flowchart.

Multimedia Appendix 3 Survey and interview questions.

## Abbreviations

BRECVEMA: brain stem reflexes, rhythmic entrainment, evaluative conditioning, contagion (emotional contagion), visual imagery, episodic memory, musical expectancy, and aesthetic judgment
DASS-21: 21-item Depression Anxiety Stress Scale
DERS: Difficulties in Emotion Regulation Scale
GHQ-12: 12-item General Health Questionnaire
MUSE: music USE
RCT: randomized controlled trial
